# Implementation of an online pain science education for chronic musculoskeletal pain in Brazilian public health system: protocol for a hybrid type III randomised controlled trial with economic evaluation

**DOI:** 10.1186/s12891-023-06360-7

**Published:** 2023-04-10

**Keywords:** Chronic pain, Health education, Telehealth, Primary healthcare, Public health, Implementation science

## Abstract

**Background:**

Although clinical practice guidelines recommend pain education as the first-line option for the management of chronic musculoskeletal pain, there is a lack of pain education programmes in healthcare. Thus, digital health programmes can be an effective tool for implementing pain education strategies for public health. This trial will aim to analyse the implementation and effectiveness outcomes of three online pain science education strategies in the Brazilian public health system (SUS) for individuals with chronic musculoskeletal pain.

**Methods:**

We will conduct a hybrid type III effectiveness-implementation randomised controlled trial with economic evaluation. We will include adult individuals with chronic musculoskeletal pain, recruited from primary healthcare in the city of Guarapuava, Brazil. Individuals will be randomised to three implementation groups receiving a pain science education intervention (*EducaDo*r) but delivered in different modalities: group 1) synchronous online; group 2) asynchronous videos; and group 3) interactive e-book only. Implementation outcomes will include acceptability, appropriateness, feasibility, adoption, fidelity, penetration, sustainability, and costs. We will also assess effectiveness outcomes, such as pain, function, quality of life, sleep, self-efficacy, and adverse effects. Cost-effectiveness and cost-utility analyses will be conducted from the SUS and societal perspectives. The evaluations will be done at baseline, post-intervention (10 weeks), and 6 months.

**Discussion:**

This study will develop and implement a collaborative intervention model involving primary healthcare professionals, secondary-level healthcare providers, and patients to enhance self-management of chronic pain. In addition to promoting better pain management, this study will also contribute to the field of implementation science in public health by generating important insights and recommendations for future interventions.

**Trial registration:**

ClinicalTrials.gov (NCT05302180; 03/29/2022).

## Contributions to the literature

Pain science education is effective for chronic musculoskeletal pain; however, there is a lack of specialised pain care in the public health system, especially in low- and middle-income countries.The literature is scarce on implementation trials testing innovative digital health solutions for healthcare.The implementation of the pain science education strategies in the Brazilian public health system (SUS) could provide information to discuss the best strategy and mode of delivery and will support the expansion of the implementation science in public health.

## Background

Chronic pain is commonly described as pain that lasts or recurs for longer than three months [1]. Most cases of chronic pain occur in the musculoskeletal system, such as osteoarthritis, back and neck pain [2]. The worldwide prevalence of chronic musculoskeletal pain is estimated at 30% in the adult population [3]. Musculoskeletal disorders are the top-ranked causes of years lived with disability (YLDs), accounting for 149 million of YLDs in 2019 globally [2]. The treatment of chronic musculoskeletal pain consists of reducing pain, maximizing function, and improving quality of life [4, 5]. Clinical guidelines commonly recommend non-pharmacological approaches as first-line management, such as exercises, manual therapies and pain education [6–9].

Pain science education provides knowledge and strategies for changing maladaptive beliefs and behaviours in face of pain, such as pain-related fear and avoidance [10, 11]. Pain science education, as one part of recommended multi-modal treatments, is effective in reducing pain [12, 13], anxiety, depression [13] and disability [14, 15], and in increasing knowledge about pain [15] in adults with chronic musculoskeletal pain. In addition to exercise-based treatment, pain science education is more effective in reducing pain (weighted mean differences: -2.09/10; 95%CI: -3.38 to -0.80) and disability (standardized mean difference: -0.68; 95%CI: -1.17 to -0.20), compared to exercise alone in the short-term [16]. Usual physiotherapy or exercise-based treatments alongside pain science education also can be cost-effective compared to usual care alone [17, 18].

Despite that, generally, evidence-based practice is inadequately integrated into lifestyle behaviours of individuals with chronic musculoskeletal pain [19–22]. Also, health policy and healthcare services deliver the treatments at a suboptimal level compared to the chronic musculoskeletal pain burden [19–22]. There is limited access to healthcare specialized in pain and health information [23], lack of skills among health workers for treating pain [5, 19, 24, 25], and limited options for biopsychosocial interventions in relation to the health system demand [26], and inadequate support for optimizing self-care [5, 24, 25]. In this context, the use of digital interventions to provide support for self-care management of health conditions attracts attention [27–29].

However, the literature is scarce in reporting the process and the outcomes of the implementation of interventions in digital models [20, 30]. Furthermore, evidence of chronic musculoskeletal pain clinical guidelines is derived largely from research on high-income economies [30]. Thus, Implementation research to bring the chronic musculoskeletal pain clinical guidelines into policy and ‘real-world’ practice in low- and middle-income countries is urgently needed.

The implementation of an online pain science education programme in Brazil can provide helpful information for low- and middle-income countries.

Therefore, the primary aim of this study is to investigate the implementation outcomes and effectiveness of three implementation strategies of an online pain science education programme in the Brazilian public health system of Guarapuava city. The second aim is to determine the cost-effectiveness of such strategies.

## Methods/ design

### Elaboration protocol

This clinical trial protocol follows the recommendations of Standard Protocol Items: Recommendations for Interventional Trials (SPIRIT) [31] (Fig. 1), Consolidated Standards of Reporting Trials (CONSORT) [32], Consolidated Standards of Reporting Trials of Electronic and Mobile Health Applications and online TeleHealth (CONSORT-EHEALTH) [33], Template for Intervention Description and Replication (TIDieR) [34], and Consolidated Health Economic Evaluation Reporting Standards 2022 (CHEERS 2022) Statement [35]; and was planned using the implementation taxonomy proposed by Proctor (2011) [36].

**Fig. 1 Fig1:**
[figure not shown]
SPIRIT recommended content for the schedule of enrollment, interventions and assessments. Figure legend: wk: week; mo: month

### Trial design

This trial is designed as a hybrid type III effectiveness-implementation randomised controlled trial, including economic evaluation, with three arms [37].

### Ethical aspects

This study was revised and approved by the Research Ethics Committee of Universidade Estadual do Centro-Oeste (UNICENTRO/Brazil; CAAE 11,975,019.0.0000.0106; date: 07/15/2022). The protocol of this study was prospectively registered at ClinicalTrials.gov (NCT05302180; 03/29/2022).

### Brazilian Unified Health System (Sistema Único de Saúde – SUS)

The SUS is one of the largest public health systems in the world [38], covering the entire Brazilian population, and is used by about 75% of the population [39]. The SUS encompasses three levels of complexity: (1) primary healthcare (i.e., first contact, diagnosis and prevention); (2) secondary healthcare (i.e., specialised medical services, diagnostic and therapeutic support, and emergency services); and (3) tertiary healthcare (i.e., highly specialised care, surgery, cancer treatment and specific diagnosis procedures) [38, 40]. Primary healthcare is available in the entire country using the same system, but secondary and tertiary healthcare depends on each state and municipality, including the flow of users, triage processes, and organisation of the system [40].

### Guarapuava City, Parana State, Brazil

The municipality of Guarapuava is located in the Center-South region of the Paraná State, Brazil. Guarapuava has an estimated population of 183.755 inhabitants, distributed in 5 administrative districts (Entre Rios, Guairacá, Guará, Palmeirinha and Sede) [41, 42]. The city has a territorial area of 3,168.087 km^2^ (1.6% of the state of Paraná) with a population density of 53.68 inhabitants/km^2^. The Human Development Index (HDI) in 2010 was 0.731 [43] and a gross domestic product (GDP) per capita of R$ 33.914.00 in 2018 [44], similar to the Brazilian average in the same year (0.765 and R$ 32,747.00, respectively).

### Organisational settings of SUS in Guarapuava City

Guarapuava has 33 primary healthcare units from SUS. Each primary healthcare unit has a defined population under its responsibility. When someone needs to use health services, the user is screened by a primary care professional, who determines the most appropriate level of healthcare attention the user needs. If the user needs a specialised health service (e.g., therapy) the health professional requests it to the public health regulation through the municipal electronic system. Thereafter, the public health regulation schedules the specialised care in the health units accredited by SUS and the user can receive the specialised care. There are five physiotherapy centres (secondary care) in Guarapuava. In this study, all patients scheduled at any of these physiotherapy centres will also be invited to participate in the online pain science education programme (named as *EducaDor*). The health professional of the primary healthcare unit can schedule the patient for the *EducaDor* programme through the municipal electronic system. A researcher from the *EducaDor* programme will assess the participant for eligibility criteria to participate in the study (Fig. 2).

**Fig. 2 Fig2:**
[figure not shown]
Schematic representation for the referral of SUS users with chronic musculoskeletal pain to *Educador* programme

### Settings and eligibility criteria

We will invite adults (18 years or older) with chronic musculoskeletal pain living in Guarapuava, Paraná State, Brazil, who were directed to physiotherapy based-care in SUS. The eligibility criteria for participating in this study are: (1) individuals who report chronic musculoskeletal pain (> three months); (2) those who speak in Portuguese; (3) those who have a smartphone, tablet, or computer with internet access; and (4) individuals who are undergoing or have been referred for physiotherapy based-care. Participants will be included in the study after agreeing to and accepting the online informed consent form.

### Procedures and randomisation

Individuals referred to the EducaDor programme will first be contacted by a researcher ([name]; [name]) via an electronic videoconferencing system at the scheduled consultation. During this initial contact, the researcher will screen the participant for eligibility and provide information about the EducaDor programme, as well as the name of the referred physiotherapy centre. Eligible participants will receive a link to an online consent form via email or text message, which they can accept to participate. Once the consent form is accepted, one researcher will conduct the baseline assessment, and another researcher will randomly assign the participant to one of the intervention groups.

Participants included in the study will receive physiotherapy-based care and the *EducaDor* programme as per randomisation into three different modes of delivery: (1) synchronous online group; (2) asynchronous videos group; or (3) interactive e-book group. Although the three groups have the interactive e-book, the synchronous online group and the asynchronous videos group receive additional types of digital content that are accessible to participants who cannot read and/or write in Portuguese. Then, the first step of randomisation will be done for participants who cannot read and/or write in Portuguese into (1) synchronous online group or (2) asynchronous videos group. The second step of randomisation will include all other eligible participants into the three different modes of delivery: (1) synchronous online group; (2) asynchronous videos group; or (3) interactive e-book group.

One researcher ([name]) will perform a stratified block randomization within the five physiotherapy centres accredited at SUS in the city, at the ratio of 1:1, using Excel software. The randomised list will be under the custody and confidentiality of the researcher ([name]). One week before the start of the *EducaDor* programme, one researcher ([name]) will send a list of participants to the researchers responsible for the interventions ([name], [name], [name], and [name]). The intervention researchers will then contact the participants to explain the intervention according to group allocation.

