In step 3, we estimated summary statistics for the simulated distributions in each of the 32 possible sample sizes, including the probability of type I error (*α*), type II error (*β*) and power (1-*β*). In step 4 we found the minimum sample size required to achieve the pre-defined type I error (*α* ≤ 0.05 or 5%), type II error (*β* ≤ 0.20 or 20%) and power (≥ 0.80 or 80%). At this moment the suggested minimum sample size was 80 participants per group. Then, corrections for loss to follow-up and correlations amongst the five clusters (physiotherapy facilities) and repeated measurements were applied [64, 65]. The sample size simulation suggested a minimum sample size of 105 participants per group, that is, 315 participants (105 in each treatment group) in total for this study.

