#### Missing data

An intention-to-treat approach (ITT) will be used in the main statistical analyses, which will include all randomized participants. The ITT analysis aims to estimate the population’s average causal effect by considering the randomised allocation regardless of whether the participants in each group complied or not with their allocation condition [68]. A complier average causal effect (CACE) will also be used to estimate the local average causal effect within the compliers [68]. ‘Compliers’ will be considered those participants who pointed at least 17 points in the adherence questionnaire (EARS-Br) [49].

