#### Quantitative data analysis

For continuous variables, we will calculate statistics of central tendency and dispersion, such as means and, standard deviation. For categorical variables, we will describe frequencies and absolute numbers. Normality will be investigated by visual inspection of histograms. The baseline characteristics of the participants and implementation outcomes will be calculated using descriptive statistics. The differences between groups and the 95% confidence interval will be calculated using mixed models. The fixed effect term will be composed of dummy variables indicating groups, and follow-up time-points, that is, 10 weeks and 6 months after baseline, and the interaction terms composed of group and time. The estimates will be adjusted for any potential differences that might exist at the baseline. The random effect term will be composed of: (1) a correlated random intercept and slope varying the intercept for the five physiotherapy clusters and varying the slope for time points; and (2) a correlated random intercept and slope varying the intercept for repeated measurements within each cluster and varying the slope for time-points [69].

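### Non-readers cannot be allocated to the e-book arm, and no stated analysis conditions on this, so the two e-book contrasts are open to confounding by literacy

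*Protocol article*

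**What the plan says.** **Who enters.** In Settings and eligibility criteria the language requirement is only "those who speak in Portuguese". Reading is not required, so non-readers can join.

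**How they are allocated.** Procedures and randomisation sets out two steps. In the first, "the first step of randomisation will be done for participants who cannot read and/or write in Portuguese into (1) synchronous online group or (2") the asynchronous video group. Then "The second step of randomisation will include all other eligible participants into the three different modes of delivery". The same section says that one researcher "will perform a stratified block randomization within the five physiotherapy centres accredited at SUS in the city, at the ratio of 1:1". No other ratio is given.

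**Who is analysed.** Under Missing data, an intention-to-treat approach "will be used in the main statistical analyses, which will include all randomized participants". The Economic evaluation section is also intention-to-treat.

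**How they are analysed.** Under Quantitative data analysis, "The fixed effect term will be composed of dummy variables indicating groups, and follow-up time-points", plus their interaction, with random effects for physiotherapy centre and repeated measures. One further sentence says that estimates will be adjusted for potential baseline differences, without naming a variable. Implementation outcomes, which include the 0 to 100 satisfaction score, are to be described. The economic section estimates cost and effect differences by regression and states no covariates.

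**What is collected.** Characteristics of the sample lists level of education and cognition, but not ability to read or write.

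**Planned size.** Sample size estimation gives "315 participants (105 in each treatment group) in total for this study".

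**The concern.** A participant who cannot read or write has zero probability of receiving the e-book alone. The e-book arm therefore contains no non-readers by design, and the other two arms contain all of them. If the two steps are pooled without conditioning on step, an e-book contrast combines a randomised comparison among readers with a group that sits on one side only. If literacy is related to pain, satisfaction, service use or quality of life, part of the estimated difference between delivery modes is a difference between people. A larger sample does not reduce it.

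Two of the three pairwise comparisons are exposed. They feed the primary effectiveness outcome (pain intensity) and two primary implementation outcomes (satisfaction and cost-effectiveness). If non-readers do worse, the error works against the synchronous and video arms.

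**Working it through.** **The plan's own figures.** Inputs from Sample size estimation: SD 2.3, difference 1.0, alpha 0.05 (two-sided assumed), power 0.80, loss 30%. With 80 per group the standard error is 2.3 × √(2/80) = 0.364 and power is Φ(1.0/0.364 − 1.96) = 0.785, close to the stated 0.80. The step to 105 is matched numerically by 80 × 1.3 = 104, although that contains no cluster correction. Nothing below depends on how 105 was reached.

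**Composition of the arms.** Let p be the share of non-readers among N = 315. The protocol does not give p, so 5%, 10% and 20% are assumed. Allocation is taken as equal within each step.

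- E-book arm: N(1 − p)/3, with no non-readers.
- Each other arm: N(1 − p)/3 + Np/2.
- Non-reader share in each other arm: s = (p/2) / [p/2 + (1 − p)/3].

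**Bias.** With no true arm effect, the bias in an unadjusted e-book contrast is s × g, where g is the outcome gap between non-readers and readers. The protocol does not give g either, so 1 and 2 points are assumed.

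| p | E-book n | Each other arm n | s | Bias, g = 1 | Bias, g = 2 |
|---|---|---|---|---|---|
| 5% | 99.8 | 107.6 | 7.3% | 0.07 | 0.15 |
| 10% | 94.5 | 110 | 14.3% | 0.14 | 0.29 |
| 20% | 84 | 115.5 | 27.3% | 0.27 | 0.55 |

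Example for p = 10%: s = 0.05 / (0.05 + 0.30) = 0.143.

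**Simulation check.** 3,000 simulated trials per setting, N = 315, SD 2.3, correlation 0.30 between baseline and follow-up, no arm effect, no loss, and the gap present at both times. For synchronous versus e-book:

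| p | Type I error, unadjusted (g = 1; g = 2) | Mean bias, unadjusted (g = 1; g = 2) | Mean bias, adjusted for baseline pain only (g = 1; g = 2) |
|---|---|---|---|
| 5% | 4.9%; 7.3% | 0.07; 0.14 | 0.05; 0.10 |
| 10% | 7.6%; 13.4% | 0.15; 0.28 | 0.11; 0.18 |
| 20% | 11.9%; 33.6% | 0.27; 0.54 | 0.19; 0.34 |

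Adjusting for baseline pain alone leaves about two thirds of the bias. Adding a literacy term, or restricting to readers, brought the mean bias to within 0.01 of zero and type I error to 4.0% to 5.3%. The two remedies agreed almost exactly. In a two-arm e-book contrast the non-readers are all in one arm, so they inform only the literacy coefficient.

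**Power of the e-book contrasts among readers.** 30% loss, no cluster correction, n per arm = 0.7 × 315(1 − p)/3:

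- p = 0 (105 per arm): 73.5 analysed. SE = 2.3 × √(2/73.5) = 0.379, power about 0.75.
- p = 5%: 69.8 analysed, power 0.73.
- p = 10%: 66.2 analysed, power 0.71.
- p = 20%: 58.8 analysed, power 0.66.

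**The case against.** The best defence is the sentence on adjusting for baseline differences. A literacy imbalance between arms is such a difference, reading status must be known before allocation, and a covariate list is commonly left to an analysis plan that is not shown here. If randomisation step were entered under that sentence, the confounding would be removed. So a reader might infer that the e-book contrasts are certain to be confounded, but the document does not support that. It does not exclude a step term; it fails to require one. The defence stops there: the sentence names no variable, reading ability is not listed as collected, education is only a proxy, and the sentence does not visibly reach the descriptive satisfaction score or the economic regressions.

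Three other stronger readings should also be set aside.

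- **That physiotherapy centre is the only stratum.** At allocation the two steps already separate non-readers from readers. What is missing is the matching term or restriction in the analysis.
- **That the e-book contrasts are not randomised at all.** Every step-2 participant is randomised across three arms, so a valid comparison exists within the data.
- **That two steps cannot yield 105 per arm.** This holds only for equal allocation within steps. At 10% non-readers, allocating step 2 as 105 / 89.25 / 89.25 and adding 15.75 non-readers to each of the last two gives 105 throughout. The document states no such ratio, and it calls its figure a minimum.

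Materiality is also open. Entry needs an internet device and acceptance of an online consent form, which may keep the share of non-readers low. At 5% and a 1-point gap the bias is 0.07 points, with no visible inflation of type I error.

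**Conclusion.** The concern holds as a defect of the stated analysis. The allocation rule makes literacy differ between the e-book arm and the other two by design, and no stated analysis is bound to condition on it. Followed as written, synchronous versus e-book and video versus e-book are open to confounding by literacy in pain, satisfaction, costs and quality-adjusted life-years. Synchronous versus video is unaffected, because both arms are open to everyone.

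The size cannot be fixed from the document. For an assumed 5% to 20% non-readers and a 1-point gap, the bias is 0.07 to 0.27 points against a target of 1.0; for a 2-point gap it is 0.15 to 0.55. It is negligible at the low end and material at the high end. These figures assume equal allocation within each step and no other adjustment.

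The single ratio of 1:1 and the equal arm sizes are secondary. The ratio does not describe a three-arm step, and equal allocation within steps gives about 94.5/110/110 at 10% non-readers. These are points to clarify, not proof that the target cannot be met.

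**What to change.** 1. Record randomisation step (or ability to read and write) as a baseline variable for every participant.
2. Base both e-book contrasts on step-2 participants. This respects intention to treat, since the step is settled before allocation. At minimum, include step as a fixed effect.
3. For synchronous versus video, keep both steps and include a step term.
4. Apply the same rule to pain, satisfaction, the complier analysis, the subgroup analysis and the economic regressions.
5. State the allocation ratio separately for each step, and replace 105 per arm with the arm sizes expected under an assumed range of non-reader shares.

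The cost is wording, one variable that must already be known at allocation, and some precision. After 30% loss and without cluster correction, power for the e-book contrasts is about 0.71 at 10% non-readers and 0.66 at 20%, against about 0.75 with 105 per arm. In a two-arm e-book contrast a step term does not avoid this loss, for the reason shown in the working. The e-book contrasts would then apply to people who can read and write, the only group to whom the protocol offers the e-book alone.
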